### 2.4. Interventions

The intervention will be the implementation, or not, of oral prophylactic techniques. The control group will continue its usual oral hygiene practice. For the study group, the oral prophylactic intervention will consist of provision of specific package including soft-bristled manual toothbrush, toothpaste, and a kit of calibrated interdental brushes (IDBs) (Curaprox CPS; Curaden) of sizes corresponding to the diameter of their interdental spaces. The participants will be instructed to brush their teeth twice-daily and to realize daily interdental brushing until delivery. The instructions for the use of the toothbrush and IDBs comprised verbal instructions supported by practical demonstration. The first use of the material will be conducted under the supervision of a qualified public health professor.

Our research is a pragmatic study that does not want to interfere with the organization of care provided during obstetrical visits. In the public health systems, except for very punctual dental emergencies, no periodontal care is suggested or provided. 

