#### 2.6.1. Pre-Screening and Assessment for Eligibility

Participants will be screened at their first prenatal visit. If they meet the eligibility criteria, the study will be presented to them. If they agree to participate and consent to be screened, the inclusion visit will be scheduled at 3 months of pregnancy.

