#### 2.6.2. Inclusion, Prenatal Examination, Oral Examination, and Baseline Interdental Microbiota Sampling (T1)

Participants will sign the informed consent form. A clinical obstetric and oral examination, followed by interdental microbiota sampling, will be performed for all participants.

Prenatal clinical examination

The obstetric clinical examination will include the measurement of weight, height, blood pressure, and the uterine height of the participants.

Biological analysis

The biological analysis will determine the level of red blood cells, white blood cells, neutrophils, C-reactive protein, creatinine, blood sugar, uremia, and proteinuria.

Oral clinical examination and sampling of the interdental microbiota

Two calibrated periodontists per site, properly trained before the beginning of the study, and who will be blinded regarding the group category at the time of the evaluation, will perform the periodontal assessment of all patients. Calibration of examiners will include a group of 32 experienced dentists. Intraclass correlation coefficients for PD and CAL will be calculated at the site level. The intra- and inter-examiner coefficients for CAL will range between 0.80 and 0.85, and between 0.75 and 0.85 for PD, respectively.

For all participants, the same four interdental sites (15–16, 25–26, 35–36, and 45–46) will be assessed; the interdental spaces between molars and premolars are the most susceptible to gingival inflammation [30,31]. The interdental diameter will be determined using a graduated conical probe—the CURAPROX IAP calibration probe (Curaden, Kriens, Switzerland) [32]. The working portion includes colored bands from the tip to the base corresponding to IDBs by increasing diameter. The largest section of each colored band corresponds to the cleaning efficiency diameter of the respective brush. This will make it possible to select the calibrated IDB (Curaden) appropriate to the diameter of the interdental space. Each previously selected tooth will be isolated using sterile cotton rolls, and the interdental biofilm will be removed using this sterile IDB. For each sample, the IDBs will be placed in 1.5 mL sterile microcentrifuge tubes and stored at 4 °C until further analysis.

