#### 2.6.3. Follow-Up Visits

Visits will be made according to the pregnant woman’s monthly follow-up schedule (Table 1). Obstetric clinical examination, biological analysis, and oral clinical examination will performed at each visit. Interdental sampling will be realized for all participants at 6 and 8 months of gestation. 

Participants in the intervention group will be asked about compliance with the study treatment (control of hygiene methods and techniques, and acceptance).

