Secondary analyses will also be performed comparing, as at randomization, the: (i) evolution of the pathogenic bacterial load of the interdental microbiota in the pregnant women intervention group compared to the control group, (ii) evolution of clinical signs of periodontal conditions in the pregnant women intervention group compared to the control group, and (iii) effect of individual oral prophylaxis during pregnancy on the risk of adverse perinatal outcomes. For dental clinical outcomes, mean and median values of clinical parameters for all oral, lingual/palatal, and proximal sites will be calculated per patient. Variations between the first and follow-up visits will be calculated.

Microbiological variables will be presented as total anaerobic counts, frequency of detection of target pathogens, counts of each pathogen studied, and proportions of each pathogen in the total microbiota. Total anaerobic counts will be log-transformed to match a normal distribution. 

The Shapiro–Wilk goodness-of-fit test and box plots will be used to determine the normal distribution of quantitative variables. Differences between groups at baseline and at follow-up visits will be determined by paired t-test or Mann–Whitney U tests for quantitative outcomes. In addition, clinical variables will be compared to repeated measures by ANOVA with Bonferroni post hoc correction controlling for visit for within-group comparisons, group (intervention or control) for between-group comparisons, and interaction between amenorrhea time and group. 

Results will be considered statistically significant at *p* < 0.05.

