## Figures and Tables

**Figure 1 mps-04-00061-f001:**
[figure not shown]
Flow chart diagram.

**Table 1 mps-04-00061-t001:** Participation timeline of the trial.

Date of Pregnancy Procedures/Visits	Timeline							
	T0	T1	T2	T3	T4	T5	T6	T7
		3 Months *	4 Months	5 Months	6 Months	7 Months	8 Months	9 Months
Pre-screening	X							
Eligibility screening	X							
Informed consent	X							
Obstetric examination	X	X	X	X	X	X	X	X
*weight*	X	X	X	X	X	X	X	X
*blood pressure*	X	X	X	X	X	X	X	X
*uterine heigh*	X	X	X	X	X	X	X	X
Biological analysis	X	X	X	X	X	X	X	X
*red blood cells*	X	X	X	X	X	X	X	X
*white blood cells*	X	X	X	X	X	X	X	X
*neutrophils*	X	X	X	X	X	X	X	X
*C-reactive protein*	X	X	X	X	X	X	X	X
*creatinine*	X	X	X	X	X	X	X	X
*blood sugar*	X	X	X	X	X	X	X	X
*uremia*	X	X	X	X	X	X	X	X
*proteinuria*	X	X	X	X	X	X	X	X
Oral examination	X	X	X	X	X	X	X	X
*pocket probing depth*	X	X	X	X	X	X	X	X
*clinical attachment loss*	X	X	X	X	X	X	X	X
*plaque index*	X	X	X	X	X	X	X	X
*gingival index*	X	X	X	X	X	X	X	X
*bleeding on interdental brushing*	X	X	X	X	X	X	X	X
Interdental microbiota analysis		X			X		X	

* Date of pregnancy.

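### The ANOVA group term named as the between-group comparison for the periodontal outcomes is diluted by one seventh to one quarter if the scheduled pre-intervention visits enter it

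*Protocol article*

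**What the plan says.** The secondary analyses in section 2.10.3 of the protocol article state that "clinical variables will be compared to repeated measures by ANOVA with Bonferroni post hoc correction controlling for visit for within-group comparisons". The sentence then gives the remaining terms: "group (intervention or control) for between-group comparisons, and interaction between amenorrhea time and group". The group main effect is thus the term assigned to the comparison of the arms. The sentence does not list the visits that enter, and it does not say whether raw values or changes are analysed.

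Table 1 has a row "Oral examination". Probing depth, attachment level, plaque index, gingival index and bleeding on interdental brushing are marked at all eight time points, T0 to T7. Section 2.6.1 places T0 before inclusion: "the inclusion visit will be scheduled at 3 months of pregnancy". The heading of section 2.6.2 ties the baseline microbiota sampling to T1. Section 2.6.3 covers the later months: "Obstetric clinical examination, biological analysis, and oral clinical examination will performed at each visit".

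Section 2.4 asks participants in the intervention arm to "realize daily interdental brushing until delivery", without naming the visit at which this begins. Section 2.5.2 defines the secondary outcomes as changes from baseline.

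**The concern.** In a balanced repeated-measures ANOVA the group main effect is the unweighted mean, over the visits in the model, of the visit-specific arm differences. A visit made before the intervention has an expected arm difference of zero, so each such visit pulls the mean towards zero. It also brings in whatever baseline imbalance randomization of only 16 clinics has left. The result is neither the post-intervention arm difference nor a change from baseline, which is what section 2.5.2 asks for.

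The periodontal outcomes carry the mechanism claim in the abstract, that daily oral hygiene reduces periodontal disease. If the term labelled as the arm comparison is diluted, a real periodontal effect would be reported as smaller than it is and tested with less power. It could also disagree with the mixed model that the same section plans for continuous outcomes, and the article does not say which of the two prevails.

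**Working it through.** The article gives no figure for this analysis, so there is none to reproduce.

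**Inputs**
- Oral examinations: 8, at T0 to T7 (Table 1).
- Follow-up visits after baseline: 6, at T2 to T7 (Table 1, section 2.6.3).
- Visits before the intervention: T1 as baseline visit (section 2.6.2), and T0 if the Table 1 entry is followed. This assumes that the intervention starts after the T1 examination.
- Clinics: 16, with 55 women each (section 2.8), so 8 clinics per arm.

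**1. Dilution.** With b pre-intervention visits and 6 follow-up visits:

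group term / mean post-intervention difference = 6 / (6 + b)

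| Visits in the model | b | Ratio | Understatement |
|---|---|---|---|
| T2–T7 only | 0 | 6/6 = 1.00 | 0% |
| T1–T7 | 1 | 6/7 = 0.857 | 14.3% |
| T0–T7 | 2 | 6/8 = 0.75 | 25% |

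Against the mean post-intervention difference these ratios hold for any time course. A simulation with a constant true effect of 1 gave 0.86 (T1–T7) and 0.75 (T0–T7).

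**2. Comparison with the effect at T7.** This depends on an assumed time course. If the effect builds linearly to 1 at T7, the sum over T2–T7 is (1+2+3+4+5+6)/6 = 3.5. The T0–T7 group term is 3.5/8 = 0.44 of the T7 effect, but the mean over T2–T7 is itself only 3.5/6 = 0.58 of it, and 0.4375/0.583 = 0.75 again. If the effect instead wanes to half by T7, the T0–T7 group term exceeds the T7 effect by 12.5%. The T7 comparison is therefore no measure of the defect.

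**3. Interaction term.** For an effect that starts at T2 and stays constant, the contrast of mean post minus mean pre recovers 100%. The article does not specify that contrast. With time entered as linear over eight visits, the squared correlation between the step pattern (0,0,1,1,1,1,1,1) and time is 0.571, so the linear term carries 57% of the information in that contrast. With time as categories, the interaction is an omnibus test on 7 degrees of freedom.

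**4. Illustrative power.** Assumed: constant effect of 0.3 SD, within-woman correlation 0.5, two-sided 5%, t with 16 − 2 = 14 df. The clinic ICC of 0.03 is borrowed from the sample-size statement for pre-eclampsia (section 2.7). The variance of 1 per visit then splits into clinic 0.03, woman 0.47 and residual 0.50. For a mean over k visits:

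Var = (2/8) × [0.03 + (0.47 + 0.50/k)/55]

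| Visits | k | Expected difference (SD) | SE | Ratio to SE | Power |
|---|---|---|---|---|---|
| T0–T7 | 8 | 0.75 × 0.3 = 0.225 | 0.0996 | 2.26 | 56% |
| T1–T7 | 7 | 0.857 × 0.3 = 0.257 | 0.0998 | 2.58 | 67% |
| T2–T7 | 6 | 0.300 | 0.1001 | 3.00 | 80% |

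The standard error hardly changes, because the clinic component dominates it, so the power loss comes almost wholly from the diluted numerator. Relative to T2–T7, the information is about 0.56–0.58 (T0–T7) or 0.74–0.75 (T1–T7) over ICC 0.01–0.05 and within-woman correlation 0.3–0.7. No row includes baseline adjustment.

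**The case against.** The strongest reply is that the dilution rests on an inference. The article does not say that T0 and T1 enter the ANOVA. The same paragraph group promises that "Variations between the first and follow-up visits will be calculated", and if those changes are the variable analysed, no baseline value is in the outcome and nothing is diluted. This stands, and it is why the point is conditional. It does not remove the point: the ANOVA sentence speaks of clinical variables and visits, and nothing in it restricts them to changes or to follow-up.

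Second, T0 may not be a true periodontal visit. Section 2.6.1 describes no oral examination there; only Table 1 marks one. On that reading the worst case is one seventh. This also stands.

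Third, the ANOVA is introduced as an addition, its own sentence contains the time-by-group interaction, and section 2.10.3 also plans visit-specific comparisons and a mixed model with a clinic random effect. These can carry the undiluted effect. That limits the harm. But the interaction is not the term assigned to the arm comparison, its useful contrast is not defined, and no order of precedence among the analyses is given.

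Fourth, the power figures use an effect size and a within-woman correlation found nowhere in the article, an ICC stated for another outcome, and a two-sided test although section 2.10.3 plans one-sided analysis. They are illustration only.

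A reader might infer that the effect is understated by at least a quarter, or that a real benefit will be missed. The article supports neither. A quarter is the ceiling against the mean post-intervention difference, and the companion analyses could still show the benefit.

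**Conclusion.** The point holds in conditional form. The article names the group main effect as the between-group comparison and does not exclude the pre-intervention examinations that its own schedule contains. If they enter, and the intervention starts after the T1 examination, the term understates the mean post-intervention arm difference by one seventh (T1 only) to one quarter (T0 and T1). Chance baseline differences between clinics then form part of the estimate. If only follow-up visits or changes are modelled, there is no understatement.

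The bias in expectation is towards zero, so it does not manufacture a benefit. It concerns secondary outcomes and leaves the primary outcome untouched. The correction is worth making because it replaces the named term with one that answers the stated question, at no cost in data.

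**What to change.** In the secondary analyses of section 2.10.3, replace the ANOVA group term as the between-group comparison of the periodontal variables:

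- Take T2 to T7 as the repeated outcomes.
- Keep T0 and T1 out of the outcome vector. Enter the baseline value as a covariate, and state whether it is T1 or the mean of T0 and T1, in place of the unspecific first visit.
- Fit this in the mixed model that section 2.10.3 already plans, with clinic as a random effect, and add a within-woman effect for the repeated visits.
- Report the average arm difference over T2 to T7 as the single between-group test for each outcome, with visit-specific differences as description.
- State at which visit the intervention begins relative to the T1 examination, and reconcile Table 1 with section 2.6.1 on whether an oral examination takes place at T0.

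The cost is a change of wording. It needs no new data, visits or participants.

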### 2.11. Ethics Statement

The protocol and design of this study have been endorsed by ethical and regulatory authorities and will be carried out in conformance with the Declaration of Helsinki. The ethical committee of Ougadoudou (Burkina Faso) approved the protocol on 10 March 2021 (2021-03-077), and the ethical committee of Dakar (senegal) approved it on 8 June 2021 (000086/MSAS/CNERS/SP). This study was registered at ClinicalTrials.gov (identification number NCT04989075).

## 3. Expected Results

As the conditions for professional prophylaxis or other types of oral health care are not practically provided in the specific context of the public system, our work will support the need for a community-based approach with a willingness to include individual prophylaxis as part of the overall primary health care. The implementation of evidence-based, individual preventive care linked to behavioral changes in oral hygiene quality will reduce PE. This comprehensive trial is a very important topic to evaluate novel strategies for preventive approaches in PE.

## Figures and Tables

**Figure 1 mps-04-00061-f001:**
[figure not shown]
Flow chart diagram.

**Table 1 mps-04-00061-t001:** Participation timeline of the trial.

Date of Pregnancy Procedures/Visits	Timeline							
	T0	T1	T2	T3	T4	T5	T6	T7
		3 Months *	4 Months	5 Months	6 Months	7 Months	8 Months	9 Months
Pre-screening	X							
Eligibility screening	X							
Informed consent	X							
Obstetric examination	X	X	X	X	X	X	X	X
*weight*	X	X	X	X	X	X	X	X
*blood pressure*	X	X	X	X	X	X	X	X
*uterine heigh*	X	X	X	X	X	X	X	X
Biological analysis	X	X	X	X	X	X	X	X
*red blood cells*	X	X	X	X	X	X	X	X
*white blood cells*	X	X	X	X	X	X	X	X
*neutrophils*	X	X	X	X	X	X	X	X
*C-reactive protein*	X	X	X	X	X	X	X	X
*creatinine*	X	X	X	X	X	X	X	X
*blood sugar*	X	X	X	X	X	X	X	X
*uremia*	X	X	X	X	X	X	X	X
*proteinuria*	X	X	X	X	X	X	X	X
Oral examination	X	X	X	X	X	X	X	X
*pocket probing depth*	X	X	X	X	X	X	X	X
*clinical attachment loss*	X	X	X	X	X	X	X	X
*plaque index*	X	X	X	X	X	X	X	X
*gingival index*	X	X	X	X	X	X	X	X
*bleeding on interdental brushing*	X	X	X	X	X	X	X	X
Interdental microbiota analysis		X			X		X	

* Date of pregnancy.

## Data Availability

No new data were created or analyzed in this study. Data sharing is not applicable to this article.
